### Baseline characteristics of the eligible subjects

Based on the results of their health examination in 2010, 19, 724 subjects met the inclusion criteria including 10, 423 males and 9, 301 females. The average age of the participants was 40.1 ± 13.1 years (range, 14 to 92 years). Baseline characteristics are presented in Table 2. The required minimum sample size was guaranteed. Individuals aged from 35–75 years were asked if he or she would participate in their scheduled annual health check-ups.

**Table 2 T2:** Baseline characteristics of eligible study participants

**Variables**	**NN**	**PN**	**NH**	**PH**
n	8542	8687	917	1578
Age ($\bar{x}\pm s$, yrs)	37.1 ± 11.4	42.7 ± 13.9	38.3 ± 12.0	42.7 ± 14.1
Gender (Male %)	39.8	60.6	63.1	75.1
BMI ($\bar{x}\pm s$, kg/m^2^)	22.8 ± 3.1	24.8 ± 3.4	24.5 ± 3 .3	26.5 ± 3.4
Waist circumstance ($\bar{x}\pm s$, cm)	75.2 ± 13.2	82.2 ± 10.4	81.5 ± 10.4	87.5 ± 9.9
Sbp ($\bar{x}\pm s$, mm Hg)	106.7 ± 6.9	124.3 ± 6.4	108.2 ± 6.4	124.7 ± 6.6
Dbp ($\bar{x}\pm s$, mm Hg)	67.7 ± 5.7	78.4 ± 5.7	68.9 ± 5.4	79.2 ± 5.5
Serum uric acid ($\bar{x}\pm s$, mg/dl)	4.7 ± 1.0	5.0 ± 1.1	7.3 ± 0.8	7.5 ± 0.9
Total cholesterol ($\bar{x}\pm s$, mg/dL)	4.9 ± 0.9	5.2 ± 1.0	5.3 ± 1.0	5.4 ± 1.0
Triglycerides ($\bar{x}\pm s$, mg/dL)	1.1 ± 0.9	1.5 ± 1.3	1.9 ± 1.4	2.2 ± 1.7
LDL ($\bar{x}\pm s$, mg/dL)	3.1 ± 0.8	3.3 ± 0.9	3.4 ± 0.9	3.3 ± 0.9
HDL ($\bar{x}\pm s$, mg/dL)	1.4 ± 0.3	1.4 ± 0.3	1.3 ± 0.3	1.3 ± 0.3
Fasting glucose ($\bar{x}\pm s$, mg/dL)	4.7 ± 0.8	4.9 ± 1.1	4.9 ± 1.0	5.0 ± 0.9
Diabetes (%)	1.8	4.1	3.2	4.0

*Normaltension and no-hyperuricemia (NN), Prehypertension and no-hyperuricemia (PN), normaltension and hyperuricemia (NH)and Prehypertension and hyperuricemia (PH).

The prevalence of prehypertension and hyperuricemia was 52.0% (n = 10,265) and 12.6% (n = 2495), respectively. The prevalence of prehypertension was higher for male (61.9%) than that for female (41.0%, chi-square = 854.0, p < 0.001). The prevalence of hyperuricemia was higher for male (16.9%) than that for female as well (7.9%, chi-square = 365.5, p < 0.001). Overweight and obese subjects had a high prevalence of prehypertension (65.0% and 78.6% in male; 55.5% and 70.6% in female). Subjects with abdominal obesity were more likely to have high-normal blood pressure than subjects without abdominal obesity (56.5% vs. 75.4% in male and 37.8% vs. 69.2% in female). Subjects with hyperuricemia had a higher prevalence than subjects without hyperuricemia (60.8% and 67.2% in male; 40.0% and 53.8% in female) (Table 3). The association of prehypertension with age was stronger for female than male as the odds ratio was 1.01 (95% CI: 0.91–1.09), 2.71 (95% CI: 2.12–3.48) for middle and old age male groups and 1.93 (95% CI: 1.76–2.12), and 7.29 (95% CI: 5.40–9.83) for middle and old age female groups. Hyperuricemia was significantly associated with prehypertension independent of the age group, BMI, and abdominal obesity among female subjects in a forward multiple logistic regression analysis, however this was not the case among the male subjects (Table 4).

**Table 3 T3:** The prevalence of prehypertension in subgroups regarding to Age, BMI, Abdominal Circumference and Hyperuricemia

**Variables**	**Male**					**Female**				
	**N**	**n**	**%**	** *χ* **^ **2** ^	** *P* **	**N**	**n**	**%**	** *χ* **^ **2** ^	** *P* **
Age group										
Young (18–34)	4066	2405	59.1	78.9	0.000	4361	1248	18.6	648.1	0.000
Middle (35–64)	5897	3674	62.3			4613	2303	49.9		
Old (65-)	460	369	80.2			327	266	81.3		
BMI										
<18.5	171	62	36.3	287.3	0.000	635	136	21.4	109.2	0.000
18.5–23.9	3528	1767	50.1			5519	1835	33.2		
24–27.9	4776	3106	65.0			2298	1275	55.5		
28-	1820	1431	78.6			676	477	70.6		
Abdominal obesity										
No	7379	4166	56.5	164.0	0.000	8268	3126	37.8	75.1	0.000
Yes	2919	2202	75.4			864	598	69.2		
Hyperuricemia										
No	8659	5263	60.8	24.4	0.000	8570	3424	40.0	53.1	0.000
Yes	1764	1185	67.2			731	393	53.8		

**Table 4 T4:** Multiple logistic regression of variables associated with prehypertension

**Variables**	**Male**		**Female**	
	** *OR* **	**95% **** *CI* **	** *OR* **	**95% **** *CI* **
Age group				
Young (18–34)	1	—	1	—
Middle (35–64)	1.00	0.91–1.09	1.93	1.76–2.12
Old (65-)	2.71	2.12–3.48	7.29	5.40–9.83
BMI				
<18.5	0.55	0.40–0.76	0.68	0.55–0.83
18.5–23.9	1	—	1	—
24–27.9	1.72	1.57–1.89	2.02	1.82–2.25
28-	2.81	2.39–3.31	3.27	2.63–4.07
Abdominal obesity				
No	1	—	1	—
Yes	1.43	1.26–1.61	1.26	1.04–1.53
Hyperuricemia				
No	1	—	1	—
Yes	Not	significant	1.39	1.18–1.64

## Discussion

Despite evidences from a number of observational studies that demonstrate a relation between serum uric acid levels and hypertension, whether treating asymptomatic hyperuricemia contributes to the prevention of hypertension is still controversial. A prospective cohort study with a nested randomised controlled trial was designed to test the hypothesis that lowering uric acid levels by dietary intervention delivered by an educational package might prevent or postpone the occurrence of hypertension. Our study is intended as an exploration for the potential practical option of preventing hypertension besides providing proof of the physiological mechanisms involved.

In this prospective cohort study, four cohorts are being followed with the diagnosis of hypertension as the endpoint for each of the participant. The first question that will be answered is whether people with hyperuricemia are more likely to process from normal or high-normal blood pressure to hypertension or not. Recent experimental and clinical evidence supports the possibility elevated uric acid levels leading to hypertension [5,8,11-14]. In another prospective nested case control study, uric acid level was not associated with an increased risk of incidence of hypertension among older men and even in the subgroup of men who were < 60 years of age, this significant association was attenuated and no longer significant after further controlling for fasting insulin, triglycerides, and total cholesterol [11].

Additionally, whether lowering of serum uric acid confers protection against the development of hypertension remains untested. Regardless of the pathophysiological explanations, the observation that a high level of uric acid was associated with hypertension implies that it is possible to prevent or postpone the onset of hypertension by reducing serum uric acid. Randomised trial data on the effect of the intervention of lowering uric acid on the prevention or treatment of hypertension would be valuable. The nested RCT aims to identify the efficacy of a uric-acid lowering education package that is characterized as a purine-restriction lifestyle intervention. These include decreasing the consumption of protein, purines, and alcohol, as well as reducing obesity. Most uric acid comes from endogenous sources, therefore, diet is considered as playing a minor role in the treatment of hyperuricemia. It is still controversial whether asymptomatic hyperuricemia should be treated by lowering uric acid medications [15]. Although the uric-acid lowering effect appeared weaker than that of uric-acid lowering drugs, other associated health benefits would make lifestyle modifications important, particularly in the high risk of hypertension population [16,17]. Lifestyle modification intervention is considered as a practical strategy for the treatment of asymptomatic hyperuricemia. Healthy lifestyle interventions would form a basic therapeutic approach not only for hyperuricemia but also for hypertension,metabolic syndrome, and cardiovascular disease, though it is not easy to promote behavioural changes. It must be noted that a small reduction in the relative risk of hypertension can translate into large public health gains considering that more than 1.6 hundred million people in China suffer from hypertension. The outcomes of the RCT include controlling the occurrence rate of hyperuricemia and the transition rate to hypertension. In addition, a comparison of the transition rate to hypertension will be performed between the controlled hyperuricemia group and the uncontrolled hyperuricemia group.

Nesting an RCT within a cohort study is less likely to damage the overall observational nature of the study [18]. On the contrary, the RCT is potentially beneficial to the health of the participants and hence, it would increase the interest and enthusiasm of the staff and participants ensuring quality control during observations and data collection. It is possible that the RCT interventions would have altered the population cohort’s integrity, but for most interventions, the bias should be no different from that found in a normal observation study. Statistical analysis of the intervention will be conducted, where appropriate. A potential bias would be in the uric-acid lowering treatment for patients with symptoms of hyperuricemia. Subjects will be asked whether he or she had uric-acid lowering treatment in the last year, and if so this will be considered as a covariate during analysis.

There are several challenges to the implementation of this study. First, subject loss during the follow-up period is problematic in most cohort studies and it often leads to bias. A simulation study identified that seriously biased estimates of the odds ratios were obtained when observations were lost during the follow-up based on missing of random mechanisms [19]. The best way of dealing with loss during follow-up is to avoid it. Some efforts were made equally for each of group to avoid loss during follow-up. The employee whose employer had a long-term annual check-up contract with our centre was given priority for enrolling in this study with the expectation of the potential for a high compliance rate. At the start of this study, the names of two or more family members or friends who do not live with our participants were asked for enrolling in the study program. Small gifts were given as financial compensation for the time lost in completing the questionnaires for this study. Full-time personnel were hired for this task. Second, selection bias is built into the cohort studies. Participants who have hyperuricemia at the baseline probably differ in other important factors that are associated with the risk of hypertension. The information on other known risk factors of hypertension was collected for stratified and multivariate analyses. Over time, the exposure status (hyperuricemia) of the study participants can change. Serum uric acid will be measured annually to identify the potential change in its level. Third, non-adherence to highly effective recommendations can lead to intervention failure. Non-adherence rate is one of the outcomes that will be evaluated. Participants will be asked whether he/she has made a lifestyle change after the intervention and the potential factors associated with non-adherence will be identified. Factors associated with non-adherence in this study will be investigated according to the information filled in the questionnaire. Measures could be developed to ensure the implementation of intervention. In addition, a potential bias would be in the uric-acid lowering treatment for patients with symptoms of hyperuricemia. Subjects will be asked whether he or she had uric-acid lowering treatment in the last year, and if so it will be considered as a covariate during analysis. Finally, as this is a single-centre study, with less attention to details results may not be replicable in other settings. With the consideration of the beneficial intervention, one could apply the findings of this single-centre study only after comparing the context of the trial with his or her situation. The subjects in this study were employed by an employer who had a long-term contract with the Health Management Centre. One should be cautious when generalizing the research results to other populations.

Hyperuricemia was associated with prehypertension in subjects screened in our centre. Hyperuricemia was associated with prehypertension, and was independent of age, body mass index (BMI), and abdominal obesity in females; however, in males it was contrary. The relationship between gender difference and the association for uric acid with blood pressure was in line with the finding of a meta-analysis of 18 prospective studies on the association between hyperuricemia and hypertension [20]. Hormonal factors might influence uric acid level and they potentially have an impact on the relationships between uric acid and blood pressure [21-23]. Further investigation of selected medical conditions, uric acid, and hormonal factors in hypertension development is warranted.

Limitations of the current study include those inherent to any study of common lifestyle factors for both hyperuricemia and hypertension. In all dietary studies focusing on individual lifestyle factors, there is the potential for confounding due to the fact that many lifestyle factors are correlated. Information of potential confounding factors including sodium intake were collected as much as we can and multivariate statistical analysis will be adopted by considering multiple risk factors. Another potential limitation would be the size of the cohorts. As noted previously, there are many potential confounding factors should be taken into account to draw meaning conclusion. The current estimated sample size might attenuate the power of this study. The sample size would be re-calculated after preliminary results were obtained from the cohorts and a sequential design was considered.

Although there are a number of observational studies that report a on the relation between serum uric acid levels and hypertension, the impact of lowering uric acid on the prevention of hypertension is still inconclusive and requires further investigation. This RCT in the cohort study will provide important data on a group of subjects who are at a high risk of developing hypertension. A clear guideline regarding the choice of treatment of asymptomatic hyperuricemia is unavailable and this study aims to provide that.

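### Forward selection left the male hyperuricemia effect without an estimate, yet the abstract and Discussion call the male result contrary and build on a sex difference that was not tested

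*Protocol article*

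**What the plan says.** The Discussion of the protocol article, and the discussion paragraph of its Abstract, state that hyperuricemia was associated with prehypertension, "independent of age, body mass index (BMI), and abdominal obesity in females; however, in males it was contrary". The Discussion then compares this difference between the sexes with a meta-analysis of 18 prospective studies and offers hormonal factors as a possible explanation.

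The result comes from the section on baseline characteristics of the eligible subjects. That section says the association was independent of the other factors in women "in a forward multiple logistic regression analysis, however this was not the case among the male subjects".

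- **Table 3 (crude):** prehypertension without and with hyperuricemia is "60.8% and 67.2% in male; 40.0% and 53.8% in female", with P printed as 0.000 in each sex.
- **Table 4 (adjusted):** women have an odds ratio of 1.39 (95% CI 1.18 to 1.64). The male entry is marked as not significant, with no odds ratio or interval.

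No test of interaction between sex and hyperuricemia is reported.

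**The concern.** Hyperuricemia is the exposure that the whole study is about. Under forward selection a variable gets an estimate only if it passes an entry rule, and in men it evidently did not. So the one number a reader needs for men, the adjusted odds ratio with its interval, is missing.

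Two statements then rest on that gap. The first is the word *contrary*, which says more than a non-significant term can show. The second is the difference between the sexes. A result that is significant in one sex and not in the other does not by itself establish a difference; that needs an estimate of the interaction.

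At stake is a conclusion that stands in the Abstract, where neither table is at hand to qualify it, and that the Discussion takes further with outside evidence and a biological explanation.

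**Working it through.** **Inputs (Table 3, subjects / prehypertensive / per cent)**

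- Men without hyperuricemia: "8659 5263 60.8", so 8659 − 5263 = 3396 without prehypertension.
- Men with hyperuricemia: "1764 1185 67.2", so 1764 − 1185 = 579 without.
- Women without: 8570 and 3424, so 5146 without.
- Women with: 731 and 393, so 338 without.

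**Reproducing the printed figures.** 5263/8659 = 60.8% and 1185/1764 = 67.2%; 3424/8570 = 40.0% and 393/731 = 53.8%. All four agree with Table 3. The Pearson chi-square for women is 53.1, as printed. For men it is 25.4 (25.1 with continuity correction) against the printed 24.4. This small discrepancy changes neither direction nor significance.

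**Crude odds ratios** (cross-product; the standard error of the log is the square root of the sum of reciprocal cell counts)

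- Men: (1185 × 3396)/(579 × 5263) = 1.32; SE = 0.0553; 95% CI 1.19 to 1.47. Risk difference 67.2 − 60.8 = 6.4 points.
- Women: (393 × 5146)/(338 × 3424) = 1.75; SE = 0.0774; 95% CI 1.50 to 2.03. Risk difference 53.8 − 40.0 = 13.8 points.

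Both are positive.

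**Crude comparison of the sexes.** The ratio of odds ratios, women to men, is 1.75/1.32 = 1.32 (95% CI 1.10 to 1.59). On the log scale, z = 0.280/√(0.0553² + 0.0774²) = 0.280/0.0951 = 2.94, p = 0.003. The crude association is weaker in men, in the same direction.

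**What *not significant* can hide after adjustment.** The adjusted male standard error is not printed. I assume 1.0 to 1.1 times the crude value. For women the corresponding ratio can be recovered: (ln 1.64 − ln 1.18)/(2 × 1.96) = 0.0840, and 0.0840/0.0774 = 1.09. I also assume a two-sided 0.05 criterion, because the article does not give the entry rule.

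- Largest non-significant male odds ratio: exp(1.96 × 0.0553) = 1.11 to exp(1.96 × 0.0608) = 1.13.
- By symmetry, the smallest is 1/1.11 = 0.90 to 1/1.13 = 0.88.
- An adjusted odds ratio of 1.05, for example, would have a 95% CI of about 0.93–0.94 to 1.17–1.18.

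The printed entry is therefore compatible with no association, a small positive one or a small inverse one. It does not distinguish them.

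**Adjusted comparison of the sexes under the same assumptions.** Setting the female 1.39 (SE 0.0840) against the largest non-significant male value:

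- z = (ln 1.39 − ln 1.114)/√(0.0840² + 0.0553²) = 2.20;
- z = (ln 1.39 − ln 1.127)/√(0.0840² + 0.0608²) = 2.03.

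Male values nearer 1.00 give larger z. A formal test would probably support a difference in strength.

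**The case against.** The strongest defence is that the article does not claim a reversal. In its sentence, *contrary* most naturally negates independence from age, BMI and abdominal obesity. The baseline section puts the same result neutrally, as not being the case in men. Table 4 says not significant rather than inverse, and the article itself prints the positive male prevalences. This stands. A reader of the Abstract alone might infer an opposite association in men; the documents do not clearly assert one, and the charge is that the wording invites it without support.

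Second, Table 3 is crude, and a positive crude association is compatible with none after adjustment. This also stands: Table 3 counts against the directional reading only.

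Third, the difference between the sexes is probably real, as the z values above suggest. This stands too. What is missing is the male estimate and the test.

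Two wider inferences are tempting and should not be drawn:

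- Table 2 gives 75.1% men in the prehypertension-and-hyperuricemia group, but that is the eligible set of 1578 people. The sample-size section requires 289 per randomised group, invitations went to people aged 35–75, and the sex mix of those randomised is not stated.
- One might expect the same selection in the cohort Cox model. The section on outcome and statistical analysis mentions none; forward selection appears only for the baseline logistic regression.

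The defence does not remove the core point: the exposure of interest was left to selection, its male estimate is not reported, and a comparison of the sexes was built on that.

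**Conclusion.** The point holds as a minor matter of reporting and analysis choice in the cross-sectional baseline analysis. Leaving hyperuricemia to forward selection cost the article its adjusted male estimate, and the Abstract and Discussion say more about men, and about the sexes compared, than the printed results support.

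In size: the crude male odds ratio of 1.32 is positive and weaker than the female 1.75. The adjusted male value is unknown. On the assumed standard error and criterion, it could be anything up to about 1.11–1.13 and still print as not significant. The data shown neither demonstrate an opposite association in men nor rule out the absence of an independent one.

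The trial's sample size, significance level and primary randomised comparison are unaffected. Nor is the trial's rationale overturned: whether the dietary intervention prevents hypertension in people with both conditions does not depend on this descriptive result.

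**What to change.** 1. Refit the two sex-specific logistic models with hyperuricemia kept in, adjusting for age group, BMI and abdominal obesity, and print the male odds ratio with its 95% CI in Table 4. All four listed variables are already in the female model, so the female 1.39 should not move if these were the only candidates.
2. Report a sex-by-hyperuricemia interaction test. Let the covariate effects differ by sex as well, because Table 4 shows very different age effects (oldest group 2.71 in men, 7.29 in women). Comparing the two adjusted log odds ratios achieves the same.
3. In the Abstract and Discussion, replace *contrary* with the estimate, for example: *no statistically significant independent association was found in males (odds ratio and 95% CI)*. Tie the remarks on sex difference to the interaction result.
4. While in Table 3, check the male chi-square of 24.4 against the printed counts, which give 25.4.

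The cost is a re-run on existing data, one table entry and two edited sentences.
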